## Abstract

**Background:**

Despite lithium’s being the most effective drug for bipolar disorder and in clinical use for decades, we still know very little about its early effects relevant to its mode of action.

**Methods/design:**

The Oxford Lithium Trial is a double-blind, randomised, placebo-controlled study of 6-week lithium treatment in participants with bipolar disorder and mood instability. Its aim is to identify early clinical, neurocognitive and biological effects. Participants (*n* = 40) will undergo an intensive battery of multi-modal investigations, including remote monitoring of mood, activity and physiology, as well as cognitive testing, fMRI and magnetoencephalography, together with biochemical and gene expression measurements to assess renal, inflammatory and circadian effects.

**Discussion:**

The findings derived from this trial may be of value in predicting subsequent therapeutic response or side effects, not only relevant to the use of lithium but also providing a potential signature to help in more rapid evaluation of novel mood stabilisers. In this respect, OxLith is a step towards the development of a valid experimental medicine model for bipolar disorder.

**Trial registration:**

ISRCTN91624955. Registered on 22 January 2015.

## Background

Bipolar disorder is a mood disorder which affects around 2 % of the population worldwide [1]. Lithium remains the only pharmacological agent primarily indicated for the treatment of bipolar disorder and has a robust evidence base for efficacy, especially in the long term [2, 3]. It also significantly reduces suicidal behaviour [4]. However, lithium treatment has serious limitations, including toxicity in overdose, many side effects and lack of efficacy in some participants [5]. New treatments are urgently needed because, despite its efficacy, many participants do not respond to or cannot tolerate lithium, or have to stop the drug due to toxicity. Moreover, the depressive episodes of bipolar disorder are difficult to treat [6] and are often prolonged, and, even when not meeting criteria for a depressive or manic episode, participants often have residual mood instability, cognitive difficulties and other complaints [7]. Despite the widespread use of lithium in bipolar disorder for over 50 years, we still know little about its mechanism of action or about the early predictors of therapeutic response. Such information would be of value, both for optimising the clinical utility of lithium and in providing potential early markers of efficacy which could be targeted in investigations of novel candidate mood stabilisers. At present, such investigations require lengthy clinical trials which are expensive and therefore risky [8, 9]. For example, the researchers in the BALANCE trial, comparing lithium, divalproex and combination lithium plus divalproex in the prevention of relapse in bipolar disorder, followed participants for up to 2 years after randomisation, starting in 2000 and reported in 2010 [10]. The field badly needs more proximal, early or intermediate outcomes that can be used reliably in early-phase trials to provide initial evidence of efficacy. Together, the absence of validated targets and the consequent difficulties of conducting clinical development programmes contribute to the dearth of therapeutic innovation in this field.

Further, as more has been discovered about the typical course of bipolar disorder, it has become clear that the definition of bipolar disorder as an episodic condition in which depression and mania are interspersed with normal mood (and its implication of normal functioning) is over-simplistic and potentially misleading [11]. More commonly, people with bipolar disorder experience prominent inter-episodic sub-syndromal mood symptoms [12, 13]. Indeed, there is increasing evidence that chronic mood instability, which persists between clinically significant mood episodes, is an important component of the clinical picture [12]. Self-reported mood instability is a risk factor for the emergence of bipolar disorder [14] and often is a disabling feature for people with bipolar disorder, particularly in those of young age or at the beginning of their illness [15]. Reactivity of mood to external events is also greater in bipolar disorder compared with other mood disorders [16]. We have demonstrated the realities of mood instability in participants, and how it can be captured longitudinally at scale and over long periods of time, using a mood-monitoring system called True Colours (https://oxfordhealth.truecolours.nhs.uk/www/en/), [17]; other groups also have provided similar evidence [18, 19]. The Oxford Lithium Trial (OxLith) will take place within our ongoing programme of research, the Collaborative Network for Bipolar Research to Improve Outcomes (CONBRIO), in which we are exploring the nature and significance of mood instability.

On the basis of these data and considerations, we hypothesise that persistent mood instability is a risk factor for clinically significant mood episodes and that better mood stabilisation may improve outcomes. If true, and if robust markers of mood instability can be identified, this raises the possibility that measuring a change in mood stability in response to lithium over a short period such as a few weeks could predict long-term therapeutic efficacy). In turn, this would be a major contribution to the development of an experimental medicine model allowing more rapid and efficient early-phase testing of novel treatments, helping to overcome the current impasse. A precedent is provided by the Oxford Emotional Test Battery (ETB) [20], which facilitates early detection of (and gives a cognitive model for) anti-depressant efficacy. The ETB is a set of emotion-related paradigms that have been shown to be sensitive to the acute effects of anti-depressants and is now in use in development programs for novel anti-depressant drugs. Importantly, the ETB works in healthy subjects as well as in participants with depression, enhancing its utility such that, if our hypothesis is correct, novel bipolar disorder treatments could also be tested in non-clinical populations selected for high mood instability.

**Fig. 1 Fig1:**
[figure not shown]
OxLith trial schedule. ECG electrocardiogram

We have designed OxLith, an innovative randomised controlled trial, to investigate the effects of lithium on mood stability and on a wide range of cognitive, neural and physiological indices. OxLith will take place within CONBRIO, a research programme funded by the Wellcome Trust, which is seeking to (1) determine the nature and significance of mood instability, its physiological correlates, and the factors influencing it; (2) find novel ways to measure mood stability in routine clinical practice using a range of measures and devices; (3) apply mathematically sophisticated methods for data analysis and interpretation; and (4) develop an experimental medicine model for mood stabilisation and bipolar disorder.

## Methods/design

The schedule for the OxLith trial is displayed in Fig. 1.

### Study objectives

The study objectives are as follows:To compare the effects of lithium and placebo on mood instabilityTo measure the cognitive effects of lithium and to look for correlations with current mood stateTo explore the effects of lithium on the variability in neural dynamics during magnetoencephalography (MEG) and functional magnetic resonance imaging (fMRI) scansTo explore the effects of lithium on physical activity and sleepTo explore the short-term effects of lithium on gene expression; circadian hormones; and thyroid, parathyroid and renal function

### Study design

The trial is designed as a single-centre, prospective, randomised, double-blind, placebo-controlled trial. Eligible participants will be randomised in a 1:1 allocation to lithium or placebo. The randomisation algorithm will minimise separately on two variables age (<25 and ≥25 years) and sex (male, female) which are related to prognosis. Routine psychiatric follow-up with be arranged outside the trial as required. Participants will be randomised following a 2-week run-in period and take the study drug for 6 weeks.

### Ethics

Written consent will be obtained from all participants. The consent form will include agreement for the results of any blood tests performed before consent to be used as baseline measures for the trial, negating the need for additional venepuncture. The study protocol was approved on 14 April 2015 by the National Research Ethics Service Committee South Central – Oxford A (reference number 15/SC/0109) and on 10 July 2015 by Oxford Health NHS Foundation Trust.

### Participants and recruitment

Participants will be recruited from the bipolar disorders research clinic in Oxford. All participants will have a diagnosis of bipolar disorder (I, II or not otherwise specified) based on the *Diagnostic and Statistical Manual of Mental Disorders, Fourth Edition,* criteria and will report clinically significant mood instability. In addition, they will be individuals for whom there is uncertainty about the benefits of lithium (for example, for an individual who has recently been diagnosed or has had relatively few major mood episodes). Participants will be aged 18 years or older; will have pre-treatment renal, cardiac, thyroid and parathyroid function acceptable for the initiation of lithium; and will be willing and able to consent to participate in the trial. Exclusion criteria include any contraindication to taking lithium, concomitant psychotropic medication which cannot be withdrawn, clinically significant substance abuse, the need for treatment of an acute mood episode where placebo would be unethical, pregnancy or being of childbearing age not using effective contraception, and current suicidal ideation.

### Interventions

The interventions are placebo or lithium carbonate 200-mg prolonged release tablets are to be taken orally at night and titrated to target serum level of 0.7 mmol/L. This dosing is consistent with routine practice.

### Measures

#### Primary outcome

The primary outcome will be mood severity and stability over the 6-week randomised period as measured using a quick inventory of depressive symptoms (16-item Quick Inventory of Depressive Symptoms–Self-Rated), the Altman Self-Rating Mania Scale and daily mood measures recorded using the short form of the Positive and Negative Affect Schedule (PANAS).

#### Secondary outcomes

##### Cognition and neural dynamics

Cognitive task performance and neural dynamics will be measured to identify the effects of lithium on physiological variability and to explore the relationship between this variability and the experience of mood instability. The outcome measures will be (1) cognitive task performance for decision making, implicit and explicit reinforcement learning (completed daily using a smart device) in relation to variability in daily measures of mood (PANAS), and (2) the results of two brain scans, one using MEG and the other fMRI. Both will include scans during resting state and whilst performing a decision-making task similar to one of the daily outcomes. Scans will be performed between 3 and 4 weeks post-randomisation when the lithium level has reached a steady state.

##### Sleep and motor activation

Participants will wear an ActiGraph monitor (ActiGraph, Pensacola, FL, USA) for the duration of the study. This will allow us to monitor daytime activity and sleep patterns.

##### Circadian system

We will monitor circadian gene expression (including *BMALL *, *PER 1* and *PER 2*) and genes targeted by lithium (e.g., *GSK3*, *IMP* and *GAD L1*) collected from the cheek. Circadian controlled hormones (cortisol and melatonin) will also be collected from saliva to explore the relationship between the circadian system, mood stability and lithium. Gene expression, melatonin and cortisol levels will all be measured every 4 h over two separate 32-h periods, one prior to randomisation and the other between weeks 3 and 4 post-randomisation.

##### Physiological effects of lithium

Blood samples will be collected pre-randomisation and at the end of the randomised phase to explore changes in a number of known biomarkers related to thyroid (thyroid-stimulating hormone, thyroid antibodies, triiodothyronine and free thyroxine), parathyroid (parathyroid hormone, calcium and vitamin D) and renal function (urea, creatinine, potassium, glomerular filtration rate, neutrophil gelatinase-associated lipocalin and cystatin C). Blood samples will also be used to explore lithium-associated changes in intracellular protein composition and structure.

### Power analysis and sample size

The target sample size is 40 participants (20 of whom will be allocated to treatment with lithium and 20 to placebo). This sample size will give more than 90 % power to detect differences between groups on the main mood outcomes at a significance level of 0.5 %. Pragmatically, this sample size is achievable.

### Blinding

All trial psychiatrists and participants will be blinded. For those participants taking placebo, sham lithium level results will be presented to the trial psychiatrist by an unblinded researcher. The sham results will be based upon information about reported adherence, time since most recent dose, and adverse events. At or just before the 6-week visit, the unblinded researcher will reveal the participant’s allocated treatment to enable the participant and psychiatrist to discuss treatment options. In the event of a medical emergency, routine care for a patient who may have been taking lithium and has symptoms consistent with lithium toxicity would be to obtain a lithium level immediately, thus negating the need for the treating doctor to be informed about the trial allocation.

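### Allocation may be disclosed shortly before the 6-week visit, so the last self-ratings in the primary outcome window may be made by participants who know their arm

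*Protocol article*

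**What the plan says.** The Blinding section of the protocol article states that "All trial psychiatrists and participants will be blinded". It then sets the point at which the blind ends: "At or just before the 6-week visit, the unblinded researcher will reveal" which arm the participant was in, the purpose being "to enable the participant and psychiatrist to discuss treatment options".

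The Primary outcome section defines the window: "The primary outcome will be mood severity and stability over the 6-week randomised period". All three instruments are completed by the participant: the "16-item Quick Inventory of Depressive Symptoms–Self-Rated", and "the Altman Self-Rating Mania Scale and daily mood measures recorded using the short form of the Positive and Negative Affect Schedule (PANAS"). The Study design section gives six weeks on study drug after a two-week run-in.

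Other measurements near the end of the window are the cognitive tasks done daily on a smart device (Cognition and neural dynamics) and the second blood sample: "Blood samples will be collected pre-randomisation and at the end of the randomised phase" (Physiological effects of lithium). The brain scans and the post-randomisation circadian sampling are placed in weeks 3 to 4.

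The article does not say whether the last ratings come before or after disclosure, or how ratings made after disclosure are handled.

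**The concern.** The participant is the rater for every component of the primary outcome. If participants learn their arm while still rating, the last entries are no longer blinded. Being told that one took lithium or placebo, just ahead of a discussion about further treatment, may itself affect mood and may do so differently in the two arms. Such a difference would enter the lithium-placebo contrast as bias.

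It could also matter for the trial's particular interest. Disclosure can produce a step in the mood series, and a step adds to within-person variability as well as to the mean. The article takes care to protect the blind by supplying sham lithium levels for placebo participants. The disclosure rule can undo that protection before the outcome window has closed.

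**Working it through.** **Which rule applies when.** The plan gives no figure for this point, so there is none to reproduce. Its power statement plays no part here. The check is one of order in time, followed by an illustration of size.

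| Item | Timing in the article | Can follow disclosure? |
|---|---|---|
| Self-rated mood (primary) | all six weeks | yes, the last entries |
| Daily cognitive tasks | daily | yes, the last entries |
| Second blood sample | close of the randomised phase | yes, but the assays are objective |
| MEG and fMRI | weeks 3 to 4 | no |
| Post-randomisation circadian sampling | weeks 3 to 4 | no |

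Disclosure ahead of the 6-week visit falls within the six-week window. Disclosure at the visit may fall before or after the last entry, because no order is set.

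**Mean mood, daily PANAS.** Inputs:
- Entries per participant: 6 × 7 = 42, one per day (from the article).
- k: days between disclosure and the last rating. This is assumed, since the article does not quantify it.
- s: shift in the between-arm difference on those days caused by knowing the arm. This is assumed to be 0.5 to 1 SD of a daily rating.

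With equally weighted entries, the exposed share is k/42 and the bias in the 6-week mean difference is s × k/42.

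| k (days) | Share exposed | Bias, s = 0.5 | Bias, s = 1 |
|---|---|---|---|
| 0 | 0% | 0 | 0 |
| 1 | 1/42 = 2.4% | 0.012 SD | 0.024 SD |
| 3 | 3/42 = 7.1% | 0.036 SD | 0.071 SD |
| 7 | 7/42 = 16.7% | 0.083 SD | 0.167 SD |

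**Mean mood, QIDS and Altman scale.** Their frequency is not stated. If they were weekly and only the last of six followed disclosure, the bias would be s × 1/6 = 0.08 to 0.17 SD. A single endpoint score taken after disclosure would carry all of s, that is 0.5 to 1 SD.

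**Stability.** Take six independent weekly ratings with unit variance and a jump of size d at the last one.
- Within-person variance rises from 1 to 1 + d²/6, so the SD is multiplied by √(1 + d²/6): 1.02 for d = 0.5 and 1.08 for d = 1.
- The mean squared successive difference rises from 2 to 2 + d²/5, because one of the five differences contains the jump. Its root is multiplied by √(1 + d²/10): 1.01 for d = 0.5 and 1.05 for d = 1.

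Both factors depend on d², so the direction of the reaction does not matter. If the arms react with equal size, even in opposite directions, the factor is the same in both and the ratio of the arms' variability is unchanged. The arm contrast is biased only if the size of the reaction differs by arm. The extreme case under these assumptions is a 1 SD jump in one arm and none in the other, which gives about 8% in the SD.

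**The case against.** The strongest reply is that a journal article condenses the full protocol, and the order of procedures within a visit belongs in that protocol or in the visit schedule. Fig. 1 and the full protocol were not available for this check and may settle it. That stands for a disclosure made at the visit. It does not cover disclosure ahead of the visit, because the article itself fixes that timing and places it inside the outcome window that it also fixes.

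A reader might infer that the last part of the primary outcome is not double-blind. The article does not support that. It permits unblinded ratings but does not prescribe them. No primary rating is said to be due at the 6-week visit, and a disclosure at the visit may well follow the last entry.

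A second reply is dilution. The primary analysis uses multiple pre- and post-randomisation measurements, and the trial describes its design as exploratory. This also stands: with a one-day gap, the bias in an average of daily PANAS is about 0.01 to 0.02 SD even for a large reaction, and a seven-day gap is hard to reconcile with the wording.

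Two other inferences go too far. The inflation of variability shown above is per person and is not a between-arm bias. The thyroid, parathyroid and renal assays are objective, so knowing the arm could affect them only indirectly, for example through a change in adherence, and nothing in the article sizes that route.

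**Conclusion.** The concern holds as a moderate one. The disclosure rule overlaps the window of a wholly self-rated primary outcome, so blinding is not secured to the end of that window. The same gap applies to the last daily cognitive tasks.

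The size cannot be fixed from the article. It rests on three things not stated: the gap between disclosure and last rating, the frequency of the QIDS and Altman scale, and the strength of the reaction. The SD units are those of a single rating, so the results should not be read as standardised effect sizes for the trial. Within those limits, an average over six weeks is little affected by a gap of a day or so. The exposure becomes material if the gap approaches a week or if the analysis relies on one late score. Once a participant has been told early, the later ratings cannot be recovered as blinded data.

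**What to change.** Remove the option of disclosing before the visit. State that allocation is revealed at the 6-week visit only after the final QIDS, Altman scale, PANAS and daily task entries have been submitted and, for consistency, the final blood sample has been drawn. Add that any rating made after disclosure is excluded from the primary lithium-placebo comparison, to cover cases where the order is broken.

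This costs a sentence or two in the protocol and a line on the visit checklist, with no added visit or staff. The only drawback is that the treatment discussion comes at the end of the same visit.

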### Statistical analysis plan

Multiple pre- and post-randomisation mood measurements will be used in an analysis of covariance model to compare lithium with placebo. Methods from the fMRIB Statistical Library (FSL) will be used to analyse fMRI data. The FSL is a software library containing image analysis and statistical tools for functional, structural and diffusion magnetic resonance imaging brain data. MEG data will be analysed using a generalised linear model (GLM) and analysis of variance. The GLM method is a standard non-linear beam former used to determine the time course of neuronal activation for each point in a predefined source space. Actigraphy data will be correlated with mood and cognitive data.

In addition to these more traditional approaches to analysis, we will apply linear and non-linear time series methods and other advanced mathematical approaches, including machine learning. These techniques can produce binary or multi-level classifications as well as point and density forecasts to quantify confidence intervals. We will also apply the mathematical theory of rough paths [21], providing a method to reduce datasets from complex non-linear systems subjected to rapidly fluctuating stimuli to their critical information, facilitating classification and prediction.

### Dissemination

Regardless of the magnitude or direction of effect, the main findings of the trial will be compiled and published in an appropriate journal and made available to participants.

## Discussion

OxLith has two main goals. The first is to better characterise the early effects and mechanism of action of lithium, together with its tolerability profile, compared with placebo. The second is to establish whether mood instability, of a higher frequency than clinical episodes of depression or mania, is sensitive to lithium. The exploratory design of OxLith is intended to provide a paradigm and generate new experimental medicine outcomes and methods which can be used to expedite the development of new medicines for bipolar disorder. Drugs such as ebselen which have effects similar to those of lithium in vitro and in available mouse models of bipolar disorder are likely early candidates for such approaches.

